| PK Assessments                      | PPK model parameters CL, V, etc.                                                                                                                                                                                                                                                                                                                                                                                                                                                                                                                                                                                                                                                                                                                                                                                                                                                                                                                                                                                                                                                                                                                                                                                                                                 |
| Sample Size                         | 
With reference to the results of the foreign study TRV130-3002, assuming that the primary efficacy variable SPID24 in the SHR8554 0.75 mg group in this study is comparable to the efficacy in the 0.35 mg group in the TRV130-3002 study, and conservatively assuming that the mean (standard deviation) of SPID24 in the low dose group of this study is 88 (45), and the mean (standard deviation) of SPID24 in the placebo group is 70 (40), it's estimated to need 118 subjects in each group by the sample size calculation formula (PASS) of comparing the means of two samples to achieve the power of 90% with <math>\alpha = 0.05</math> (two-sided), provided that the four groups are designed in a 1:1:1:1 ratio. Considering the dropout rate of 10%, each group is planned to enroll 132 subjects, with a total of 528 subjects.
                                                                                                                                                                                                                                                                                                                                                                          |
| Data Analysis / Statistical Methods | 
The general principles for descriptive statistical analysis in this study are as follows: Count data will be summarized using frequencies and percentages. Measurement data will be summarized using mean, standard deviation, median, maximum, minimum, etc. Plasma concentration data will be summarized using mean or geometric mean, standard deviation, coefficient of variation or geometric coefficient of variation, median, maximum, and minimum. SAS 9.4 will be used for calculation, and all statistical tests will be performed using two-sided tests, with <math>P \leq 0.05</math> considered as statistically significant.
 
Efficacy Analysis
 
The primary efficacy variable SPID24 will be compared between groups using analysis of variance, and SPID24 in each group will be statistically described. The high dose group and low dose group will be tested sequentially, and descriptive statistics will be performed in the morphine group. For the secondary efficacy variables, analysis of variance, chi-square test, Fisher's exact probability method, and nonparametric test will be used for difference analysis according to the nature of the data.
 
Safety Analysis
 |

|  |                                                                                                                                                                                                                                                                                                                                              |
|--|----------------------------------------------------------------------------------------------------------------------------------------------------------------------------------------------------------------------------------------------------------------------------------------------------------------------------------------------|
|  | 
The incidence of AEs and ADRs in each group will be compared using chi-square test or Fisher's exact probability method, and frequency and percentage will be used to describe the AEs and ADRs.
 
PK Analysis
 
The population PK model parameters (CL, V, etc.) will be estimated using the pharmacometric method.
 |
|--|----------------------------------------------------------------------------------------------------------------------------------------------------------------------------------------------------------------------------------------------------------------------------------------------------------------------------------------------|

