| Safety Assessments                  | 
Safety assessments will include on-study AEs, laboratory tests (hematology, blood chemistry, urinalysis, coagulation), 12-lead ECG, vital signs (blood pressure [BP], respiratory rate [RR], heart rate [HR], body temperature [T]), transdermal oxygen saturation (SpO2), and complete physical examination.
 
The following AEs need to be focused on and described statistically separately: nausea, vomiting, dizziness, and respiratory depression (respiratory depression is defined as respiratory rate < 8 beats/min and/or oxygen saturation < 90%).
                                                                                                                                                                                                                                                                                                                                                                                                                                                                                                                                                                                                                                                                       |

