### **Risks and Benefits**

According to the results of the SHR8554 Phase 1 SAD study in healthy subjects and 201P study, common adverse reactions included dizziness, nausea, and vomiting, with no SAEs or severe AEs related to the investigational product. The safety precautions established in this trial are as follows: for the treatment of drug overdose, the main focus should be placed on airway opening and auxiliary facilities and the reconstruction of controlled ventilation. If drug overdose coincides with circulatory shock and pulmonary edema, appropriate measures (including oxygenation and vasopressors) should be taken. Cardiac arrest and arrhythmias may require cardiopulmonary resuscitation and defibrillation. As an antagonist of opioid receptor, naloxone antagonizes respiratory depression caused by SHR8554 Injection or morphine, therefore, an appropriate amount of this antagonist may be considered by intravenous infusion in case of respiratory depression. The study site must be equipped with necessary medical rescue equipment, first aid drugs and emergency measures. Emergency medical events or unexpected disasters shall be handled in accordance with clinical SOPs. In addition, the investigator can decide whether other appropriate measures are required according to the actual situation. SHR8554 Injection has fewer side effects than classic MOR agonists in terms of mechanism of action and can provide another option for clinical postoperative pain management.

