PK blood sampling: three PK blood samples will be collected from each subject for plasma concentration analysis and drug metabolizing enzyme gene analysis as specified in the *Clinical Sample Operation Manual*. The PK blood sampling time points include: immediately After the end of of loading dose infusion of investigational product, and 20 min, 45 min, 1 h, 3 h, 6 h, 12 h and 24 h after the infusion (see *Clinical Sample Operation Manual* for the specific blood sampling points for each subject).

Blood samples at each time point can be collected at any time within the time window (see the *Clinical Sample Operation Manual* for the time window of blood sample collection), and the time of blood collection should be accurately recorded. If the PK sampling time coincides with the pain scoring time, the pain scoring should be performed first. Approximately 3 mL of venous blood will be collected at each collection point into K2EDTA tubes, pretreated and preserved as required until use for analysis.

The subject will be required to have continuous ECG monitoring (brief interruptions are allowed due to transit and the subjects are allowed to perform necessary activities) from 0 h to stopping the infusion of investigational product.

The investigator should perform 12-lead ECG and record the subject's vital signs (blood pressure [BP], respiratory rate [RR], heart rate [HR], body temperature [T]) and transdermal oxygen saturation (SpO2) from randomization to 0 h, and at 1 h, 2 h, 3 h, 6 h ( $\pm 5$  min as the assessment point window from 1 h to 6 h), 12 h and 24 h ( $\pm 15$  min as the assessment point window for 12 h and 24 h assessments). The investigator will decide whether additional 12-lead ECG is required according to the subject's clinical condition.

During the treatment period, the time to the first use of rescue analgesics, the cumulative amount of rescue analgesics from the end of the infusion of loading dose to 24 h, the number of treatments of rescue analgesics, the total number of PCA pump presses within 24 h, the number of effective presses of PCA pump, and the time of effective presses of PCA pump will

be recorded. Within 30 min after stopping the PCA pump at 24 h ( $\pm$  5 min), the subject and the investigator will score their satisfaction with analgesia of the investigational product, respectively.

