## Adverse Events

Assessment of AEs includes type, incidence, severity, time of onset, seriousness, and relationship. AEs that occur during the study will be recorded on the AE page of the eCRF.

The following AEs need to be focused on and described statistically separately: nausea, vomiting, dizziness, and respiratory depression (respiratory depression is defined as respiratory rate < 8 beats/min and/or oxygen saturation < 90%).

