### 7.4.2 Adverse Events

TEAEs will be coded according to the current version of MedDRA at the time of coding and processed in the statistical analysis.

- The number and incidence of treatment-emergent adverse events/treatment-related adverse events, treatment-emergent serious adverse events/treatment-related serious adverse events, and adverse events leading to withdrawal from the study/treatment-related adverse events will be summarized by SOC and PT;
- Treatment-emergent adverse events/treatment-related adverse events occurring in  $\geq 10\%$ / $\geq 5\%$  of subjects ( $\geq 10\%$ / $\geq 5\%$  in any group) will be summarized by PT;
- The number and incidence of adverse events of special interest, i.e., nausea, vomiting, dizziness, respiratory depression (respiratory depression defined as respiratory rate  $< 8$  beats/min and/or oxygen saturation  $< 90\%$ ) during the treatment period, will be summarized;

If a subject experiences multiple AEs, he/she will be counted only once in incidence calculation; if a subject experiences the same AE for multiple times, he/she will be counted only once in the incidence calculation of this AE.

AEs will be summarized in frequency tables by system organ class (SOC) and preferred term (PT). Incidence (number of subjects: number of subjects with at least one AE) will

be calculated by system and symptom/sign.

The number and incidence will be calculated by severity and relationship to study drug, SOC and PT, respectively (for AEs with repeated occurrences, the event with the worst severity will be calculated for analysis).

A listing of all AEs and SAEs experienced by the subjects will be provided.

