#### 7.4.8 Concomitant Medications and Concomitant Non-drug Therapies

The use of concomitant medications during the study and the frequency of use of each drug will be summarized. Concomitant medications will be coded by ATC classification, and frequencies will be summarized and described by Anatomical Classification (ATC Level 1 coding) and Therapeutic Classification (ATC Level 2 coding).

Concomitant non-drug therapies during treatment: the frequency and constituent ratio will be calculated.

A listing of concomitant medications and concomitant non-drug therapies used by

subjects will be provided.

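### The respiratory depression count takes no account of oxygen status or respiratory interventions, so cases held above both limits can be missed

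*Combined protocol and SAP*

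**What the plan says.** Respiratory depression is one of four adverse events picked out for separate description. Protocol 7.2 (Adverse Events) gives the rule: "respiratory depression is defined as respiratory rate < 8 beats/min and/or oxygen saturation < 90" per cent. The Synopsis has the same rule ("respiratory depression (respiratory depression is defined as respiratory rate" below 8, and/or saturation below 90%), and SAP 7.4.2 repeats it ("respiratory depression (respiratory depression defined as respiratory rate" below 8, and/or saturation below 90%). The SAP analysis is a tabulation for the treatment period: "The number and incidence of adverse events of special interest, i.e., nausea, vomiting, dizziness, respiratory depression".

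Respiratory rate and SpO2 are scheduled "from randomization to 0 h, and at 1 h, 2 h, 3 h, 6 h", then at 12 h and 24 h (protocol section 3). Protocol 7.2 standardises rest, arm and posture for vital signs but says nothing about oxygen. SAP 7.4.7 summarises SpO2 without oxygen status.

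Protocol 1.2 (Risks and Benefits) mentions respiratory interventions only as management. Airway and ventilation measures are for overdose. Where overdose coincides with shock and pulmonary oedema, "appropriate measures (including oxygenation and vasopressors) should be taken". For respiratory depression itself, the text says that "naloxone antagonizes respiratory depression caused by SHR8554 Injection or morphine".

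Interventions are recorded elsewhere. Concomitant medications go into the eCRF (protocol 5.7), non-drug therapies are collected (protocol 6.2), and the treatment of each adverse event is to be noted (protocol 8.1). SAP 7.4.8 adds: "Concomitant non-drug therapies during treatment: the frequency and constituent ratio will be calculated". No rule carries these records into the respiratory depression count.

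**The concern.** An SpO2 of 92% on oxygen and 92% on room air do not mean the same thing, yet the plan treats them alike. A subject who is supported early enough may never record a value below either limit. A low count could therefore mean little respiratory depression, or depression that was supported, and the planned tables could not tell the two apart.

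This matters because protocol 1.1 presents SHR8554 as a drug expected to cause less respiratory depression, and protocol 1.2 (Selection of Control Drug) includes morphine so that safety as well as efficacy can be compared. Events may be few, so a handful of missed cases could change how the row reads.

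**Working it through.** **1. Arm size.** The only plan figure used is 132 per arm, and it reproduces. SD = √((45² + 40²)/2) = 42.57. With a difference of 88 − 70 = 18, two-sided α 0.05 and 90% power, n = 118. Then 118/0.9 = 131.1, rounded up to 132, and 4 × 132 = 528. This calculation is for SPID24; the plan has no rate, power or sample size for respiratory depression.

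**2. Which cases the rule catches.**

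| Course | Counted? |
|---|---|
| Either limit crossed and recorded, then treated | Yes; recovery does not cancel the event |
| RR below 8, SpO2 held at 90% or more by oxygen | Yes, on the rate limb |
| RR 8 or more, SpO2 held at 90% or more by oxygen | No |
| Treated before either limit is reached | No |

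Let m be the share of true cases in the last two rows, where a true case is one that either a threshold or a respiratory intervention would show. If a share r of true cases records RR below 8, then m cannot exceed 1 − r. For example, m = 75% requires r ≤ 25%.

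**3. Effect on one arm (assumed rates).** Expected counted events = 132 × p × (1 − m). Chance of no counted event = (1 − p(1 − m))^132.

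| m | Events, p = 2.5% | P(none), p = 2.5% | Events, p = 5% |
|---|---|---|---|
| 0 | 3.30 | 0.035 | 6.60 |
| 25% | 2.48 | 0.082 | 4.95 |
| 50% | 1.65 | 0.190 | 3.30 |
| 75% | 0.83 | 0.437 | 1.65 |

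**4. Effect between arms (assumed rates).** With true rates p1 > p2 and missed shares m1 and m2, the observed difference is p1(1 − m1) − p2(1 − m2).

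- Equal shares: the difference shrinks by the factor (1 − m) and the risk ratio is unchanged. For 15% v 5%, the difference is 10, 7.5, 5 and 2.5 points at m = 0, 25%, 50% and 75%, and the ratio stays at 3.
- Half missed in the higher arm only: 7.5% v 5%, a difference of 2.5 points and a ratio of 1.5.
- Half missed in the lower arm only: 15% v 2.5%, a difference of 12.5 points and a ratio of 6.

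So the difference is understated when p1·m1 > p2·m2, and the ratio falls only when m1 > m2.

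Fisher exact power at 132 per arm (two-sided 0.05, equal shares) shows the loss of information:

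| True rates | m = 0 | 25% | 50% | 75% |
|---|---|---|---|---|
| 15% v 5% | 0.729 | 0.560 | 0.345 | 0.119 |
| 10% v 3% | 0.550 | 0.392 | 0.223 | 0.050 |
| 20% v 10% | 0.568 | 0.418 | 0.253 | 0.100 |

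This is illustration only. The Synopsis mentions chi-square or Fisher tests for adverse events in general, but SAP 7.4.2 plans number and incidence for this event.

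**The case against.** The strongest reply is that a numerical threshold is objective, and that most of what looks lost is not lost. Much of this stands, and it rules out several stronger readings that a reader might infer.

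- *That treated cases drop out.* They do not. Any recorded value below a limit meets the rule, and adverse events are collected from consent to the end of follow-up (protocol 8.1), not only at scheduled readings.
- *That oxygen defeats the whole definition.* The rule is and/or, so oxygen can mask the saturation limb but does not itself hide a rate below 8.
- *That the protocol names oxygen and ventilation as its response to respiratory depression.* Protocol 1.2 ties only naloxone to it; the other measures are for overdose or its complications.
- *That interventions go unrecorded or cannot be timed.* Medications, non-drug therapies and treatment of adverse events are recorded. SAP 7.1.4 places medication start times relative to first dose to the minute, and the non-drug table covers the treatment period. What is missing is the rule linking them to this count.
- *That the eCRF has no oxygen field.* The eCRF is not among the documents; only the silence of the protocol and SAP can be stated.

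A respiratory event that stays above both limits could also be reported as an adverse event and appear in the SOC/PT tables. Phase 2 study 201P reported decreased oxygen saturation in this way, in 1 of 11 morphine subjects (9.09%). No confirmatory claim is affected: the hypothesis test concerns SPID24, and protocol 10.5 describes the safety analysis as descriptive.

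None of this supplies oxygen status at an SpO2 reading, or brings pre-empted cases into the special-interest row.

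**Conclusion.** The point holds as a limited gap that is cheap to close. Followed as written, the special-interest count can miss cases kept above both limits by oxygen or by early treatment, so the absolute count and the arm differences may be understated.

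The size is unknown. The documents give no rate of respiratory depression and no rate of oxygen or naloxone use, and every incidence and missed share in the working is an assumption. A reader might go further and infer that the gap makes the arms look alike or pulls the risk ratio towards 1. The documents do not support that: with equal missed shares the ratio does not move, and nothing shows that the shares differ by arm or in which direction. Nor do they call respiratory depression the main opioid harm; it is one of four events of focus. The threshold definition is sound as the main row and need not be replaced.

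**What to change.** - Keep the threshold definition unchanged as the main row in SAP 7.4.2.
- Add a prespecified supplementary row by arm: subjects with a threshold event, or with any of the following after 0 h for a respiratory reason: oxygen started or increased, airway or ventilatory support, or naloxone given. Use the treatment period that 7.4.2 already uses.
- Record oxygen status (yes/no, and flow) at each scheduled RR/SpO2 reading, and show it descriptively beside the SpO2 summary in SAP 7.4.7.

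The cost is one eCRF item at readings already scheduled (seven per subject in the treatment period: pre-dose, 1, 2, 3, 6, 12 and 24 h) plus SAP wording. If readings have already been taken without it, the supplementary row could draw on the medication, non-drug therapy and adverse event records, as far as they name these interventions and the reason for them.

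The downside is that the added components depend on blinded clinician judgement and site habit, and attributing a respiratory reason may admit causes other than the opioid. The row should therefore stay supplementary and descriptive. The change concerns recording and counting only; no change to patient care is proposed.

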## Clinical Study Flow Chart

| Study Periods                                        | Screening Period                                                                                                                  | Treatment Period (from randomization to 24 h, with the time to start infusion of the loading dose of investigational product recorded as 0 h) |                                                               |                                |        |        |        |     |       |     |     |     |     |     |     |      |      |      |      | Follow-up Period |
|------------------------------------------------------|-----------------------------------------------------------------------------------------------------------------------------------|-----------------------------------------------------------------------------------------------------------------------------------------------|---------------------------------------------------------------|--------------------------------|--------|--------|--------|-----|-------|-----|-----|-----|-----|-----|-----|------|------|------|------|------------------|
| Visit (Day)                                          | From signing the ICF to randomization, with a maximum of no more than 7 days, and the day of randomization will be recorded as D1 | Before starting infusion of the loading dose of investigational product                                                                       | Start infusion of the loading dose of investigational product |                                |        |        |        |     |       |     |     |     |     |     |     |      |      |      |      | 24 h ~ D4±1      |
| Time                                                 |                                                                                                                                   |                                                                                                                                               | 0 h                                                           | Immediately after the infusion | 20 min | 30 min | 45 min | 1 h | 1.5 h | 2 h | 3 h | 4 h | 5 h | 6 h | 8 h | 10 h | 12 h | 18 h | 24 h |                  |
| Signing the ICF                                      | X                                                                                                                                 |                                                                                                                                               |                                                               |                                |        |        |        |     |       |     |     |     |     |     |     |      |      |      |      |                  |
| Eligibility criteria review                          | X                                                                                                                                 |                                                                                                                                               |                                                               |                                |        |        |        |     |       |     |     |     |     |     |     |      |      |      |      |                  |
| Medical histories                      | X                                                                                                                                 |                                                                                                                                               |                                                               |                                |        |        |        |     |       |     |     |     |     |     |     |      |      |      |      |                  |
| Demographics                                         | X                                                                                                                                 |                                                                                                                                               |                                                               |                                |        |        |        |     |       |     |     |     |     |     |     |      |      |      |      |                  |
| Complete physical examination          | X                                                                                                                                 |                                                                                                                                               |                                                               |                                |        |        |        |     |       |     |     |     |     |     |     |      |      |      |      | X                |
| ECG monitoring                         |                                                                                                                                   |                                                                                                                                               | X                                                             |                                |        |        |        |     |       |     |     |     |     |     |     |      |      |      |      |                  |
| Vital signs                            | X                                                                                                                                 | X                                                                                                                                             |                                                               |                                |        |        |        | X   |       | X   | X   |     |     | X   |     |      | X    |      | X    | X                |
| Oxygen saturation (SpO 2 )  | X                                                                                                                                 | X                                                                                                                                             |                                                               |                                |        |        |        | X   |       | X   | X   |     |     | X   |     |      | X    |      | X    | X                |
| 12-Lead ECG                            | X                                                                                                                                 | X                                                                                                                                             |                                                               |                                |        |        |        | X   |       | X   | X   |     |     | X   |     |      | X    |      | X    | X                |
| Drug abuse screening                                 | X                                                                                                                                 |                                                                                                                                               |                                                               |                                |        |        |        |     |       |     |     |     |     |     |     |      |      |      |      |                  |

| Study Periods                                   | Screening Period                                                                                                                  | Treatment Period (from randomization to 24 h, with the time to start infusion of the loading dose of investigational product recorded as 0 h) |                                                               |                                |        |        |        |     |       |     |     |     |     |     |     |      |      |      |      | Follow-up Period |
|-------------------------------------------------|-----------------------------------------------------------------------------------------------------------------------------------|-----------------------------------------------------------------------------------------------------------------------------------------------|---------------------------------------------------------------|--------------------------------|--------|--------|--------|-----|-------|-----|-----|-----|-----|-----|-----|------|------|------|------|------------------|
| Visit (Day)                                     | From signing the ICF to randomization, with a maximum of no more than 7 days, and the day of randomization will be recorded as D1 | Before starting infusion of the loading dose of investigational product                                                                       | Start infusion of the loading dose of investigational product |                                |        |        |        |     |       |     |     |     |     |     |     |      |      |      |      | 24 h ~ D4±1      |
| Time                                            |                                                                                                                                   |                                                                                                                                               | 0 h                                                           | Immediately after the infusion | 20 min | 30 min | 45 min | 1 h | 1.5 h | 2 h | 3 h | 4 h | 5 h | 6 h | 8 h | 10 h | 12 h | 18 h | 24 h |                  |
| (7)                                             |                                                                                                                                   |                                                                                                                                               |                                                               |                                |        |        |        |     |       |     |     |     |     |     |     |      |      |      |      |                  |
| Pregnancy test                                  | X                                                                                                                                 |                                                                                                                                               |                                                               |                                |        |        |        |     |       |     |     |     |     |     |     |      |      |      |      |                  |
| Infectious disease screening      | X                                                                                                                                 |                                                                                                                                               |                                                               |                                |        |        |        |     |       |     |     |     |     |     |     |      |      |      |      |                  |
| Laboratory test                   | X                                                                                                                                 |                                                                                                                                               |                                                               |                                |        |        |        |     |       |     |     |     |     |     |     |      |      |      |      | X                |
| Pain intensity score             |                                                                                                                                   | X                                                                                                                                             |                                                               | X                              | X      | X      | X      | X   | X     | X   | X   | X   | X   | X   | X   | X    | X    | X    | X    |                  |
| Pain relief score                |                                                                                                                                   |                                                                                                                                               |                                                               | X                              | X      | X      | X      | X   | X     | X   | X   | X   | X   | X   | X   | X    | X    | X    | X    |                  |
| Subject satisfaction score       |                                                                                                                                   |                                                                                                                                               |                                                               |                                |        |        |        |     |       |     |     |     |     |     |     |      |      |      |      | X                |
| Study doctor satisfaction score  |                                                                                                                                   |                                                                                                                                               |                                                               |                                |        |        |        |     |       |     |     |     |     |     |     |      |      |      |      | X                |
| Randomization                                   | X                                                                                                                                 |                                                                                                                                               |                                                               |                                |        |        |        |     |       |     |     |     |     |     |     |      |      |      |      |                  |
| Administration of investigational               |                                                                                                                                   |                                                                                                                                               | X                                                             |                                |        |        |        |     |       |     |     |     |     |     |     |      |      |      |      |                  |

| Study Periods                             | Screening Period                                                                                                                  | Treatment Period (from randomization to 24 h, with the time to start infusion of the loading dose of investigational product recorded as 0 h) |                                                               |                                |        |        |        |     |       |     |     |     |     |     |     |      |      |      |      | Follow-up Period |
|-------------------------------------------|-----------------------------------------------------------------------------------------------------------------------------------|-----------------------------------------------------------------------------------------------------------------------------------------------|---------------------------------------------------------------|--------------------------------|--------|--------|--------|-----|-------|-----|-----|-----|-----|-----|-----|------|------|------|------|------------------|
| Visit (Day)                               | From signing the ICF to randomization, with a maximum of no more than 7 days, and the day of randomization will be recorded as D1 | Before starting infusion of the loading dose of investigational product                                                                       | Start infusion of the loading dose of investigational product |                                |        |        |        |     |       |     |     |     |     |     |     |      |      |      |      | 24 h ~ D4±1      |
| Time                                      |                                                                                                                                   |                                                                                                                                               | 0 h                                                           | Immediately after the infusion | 20 min | 30 min | 45 min | 1 h | 1.5 h | 2 h | 3 h | 4 h | 5 h | 6 h | 8 h | 10 h | 12 h | 18 h | 24 h |                  |
